### Outcomes and timeline

#### Primary endpoint

Target lesion control▪ Response to treated lesions will be rated based on RANO-Criteria [19] or RECIST 1.1-Criteria.

#### Secondary endpoints

Intracranial Progression▪ Target lesion or distal brain lesion▪ Symptomatic or asymptomatic brain lesion
PFSOS▪ Neurological or non-neurological death▪ Cancer or non-cancer related deathCognitive Function▪ HVLT-R (immediate recall, delayed recall, and total recall)▪ Colour Trail Test (CTT) – a language-free version of the TMTQuality of Life (QoL)▪ Functional Assessment of Cancer Therapy with Brain Subscale (FACT-BR)▪ Euro QOL – 5 Dimension – 5 Level (EQ-5D-5L)Activities of Daily Living (ADL)▪ Barthel Index of ADLsToxicity▪ Scored using Common Terminology Criteria for Adverse Events (CTCAE) ver5.0 criteria▪ Presence of radiation necrosis (asymptomatic or symptomatic)

All time points will be taken from the time of randomisation to event. If response assessment of the target lesion(s) is uncertain or equivocal, this should be reassessed by a multi-disciplinary team for clarification. When needed, this may be followed up with advanced imaging or histology.

Cognitive function, ADL and QoL will be assessed using patient-directed questionnaires that have been validated, available in local languages and used in the trials mentioned earlier for ease of comparison. These tests are optional but encouraged for all patients and will be conducted by a trained physician or clinical research associate at specified time points (Table 3). The total duration of the combined test is estimated to be 30 min. In the analysis of cognitive function, ADL and QoL, each patient will serve as his/her own control. The test results at each follow-up (post-treatment) time point will be compared to the baseline (pre-treatment) test result.

**Table 3 Tab3:**
[figure not shown]
Schedule of Enrolment, Interventions, and Assessments Recommended Follow-up Schedule Protocol^

^The follow-up schedule is based on current recommended routine practice. A window period of +/− 2 weeks is allowed for the 1st month follow up visit. +/− 1 month is allowed for the 3rd, 6th and 12th month follow-up visit. It is advised that this be followed for standardisation of records, however individual deviations will be allowed. ^+^MRI Brain imaging if performed following surgery should be done 2-weeks post op. MRI is recommended for follow-up brain imaging but contrasted-CT scan is allowed

*Only in females with child-bearing potential

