### Eligibility criteria

Participants will be recruited if they meet the criteria set out in Table 1 below.

**Table 1 Tab1:** Eligibility Criteria

Inclusion Criteria	Exclusion Criteria
• 21–80 years old patients • Radiological confirmed brain metastases (4–25 lesions) • Histologically proven malignancy • ECOG performance status ≤2 • Maximum lesion or cavity size ≤5 cm o For patients with large (≥3 cm) lesions, a neurosurgical consult is recommended due to the increased risk of cerebral oedema o If brain surgery or other invasive procedures are performed, the treatment should begin at least 2-weeks post-procedure • Life expectancy of at least 6 months • Negative serum pregnancy test within 14 days prior to registration for women of childbearing potential • Women of childbearing potential and male participants who are sexually active must agree to use a medically effective means of birth control throughout protocol treatment • Not suitable for or does not want SRS • Agrees to be randomised to either HA-WBRT or HA-SIB-WBRT	• Prior whole brain radiotherapy. o Prior SRS is not an exclusion. Details of treatment must be recorded. • Diffuse leptomeningeal disease • Extensive extracranial disease, not controlled by systemic treatment • Major medical or psychiatric illness, which in the investigator’s opinion would interfere with the completion of therapy and follow up • Dementia, ongoing psychotic episodes or moderate-severe depression (PHQ-9). • Recent stroke in the past 3 months • Symptomatic brain metastases limiting ADLs • Rapid progression of brain lesion • Patients unable to give informed consent • Total tumour planning target volume (PTV) > 60 cc • Radiological evidence of hydrocephalus • Contraindication to Gadolinium contrast-enhanced MRI brain • Patients with diagnoses of small cell carcinoma, lymphoma or primary brain tumour

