### Interventions

The control arm in this study is HA-WBRT. This will be given 30Gy in 10 fractions.

The experimental procedure is HA-SIB-WBRT. 40-45Gy in 10 fractions will be used for the SIB boost depending on the location of the lesion. 45Gy was selected as it has a similar biological effective dose (BED 65.2Gy; α/β = 10) to the 21Gy SRS dose. 40Gy (EQD2 60Gy; α/β = 2) was selected for tumours within/ close to organs at risk (OARs) to meet the recommended dose limits of common OARs. Any post-operative cavity will be contoured using consensus guidelines [18]. The cavity will be given a boost of 40Gy due to the high risk of microscopic residual disease and tumour seeding. Any gross residual tumour should be boosted to 45Gy. Further radiotherapy dose guidance is described in Table 2.

**Table 2 Tab2:** Radiotherapy Planning targets, Organs at Risk and Dose Guidance

Volume	Description	Dose Target/ Limits	Variation Acceptable	Notes
GTV_45Gy^b^	Contoured using fused contrast enhanced MRI images.	45Gy 98% covered by 100% dose Hotspot > 110% within GTV	95% covered by 95% dose	Lesion visible on at least 2 scan slices. Coverage to be comprised to meet OAR constraints
PTV_45Gy^b^	GTV + 0-2 mm isotropic margins	45Gy 98% covered by 95% dose	90% covered by 90% dose	Coverage to be comprised to meet OAR constraints
GTV_40Gy^b^	Tumour volume within/ ≤5 mm from OAR	40Gy 95% covered by 95% dose Hotspot > 110% within GTV	90% covered by 95% dose	Lesion visible on at least 2 scan slices. Coverage to be comprised to meet OAR constraints
PTV_40Gy^b^	PTV_40Gy = GTV_40Gy; i.e. no expansion	40Gy 95% covered by 95% dose	90% covered by 90% dose	Coverage to be comprised to meet OAR constraints
GTVall_5mm^b^	All GTVs + 5 mm isotropic margins	–	–	For plan optimisation
Left & Right Hippocampus	Contoured using fused MRI as per RTOG contouring atlas (http://www.rtog.org//corelab/contouringatlases/hippocampalsparing.aspx), excluding any GTV	D100% (Dose to 100% volume) ≤ 9Gy Dmax ≤16Gy Dmax ≤33Gy^a^	D100% ≤ 10Gy Dmax ≤17Gy Dmax ≤44Gy^ab^	Dmax to 0.03 cc
Hippocampal Avoidance Zone (HAZ)	Hippocampus + 5 mm isotropic margins	–	–	For plan optimization
Left & Right Optic chiasm	–	Dmax ≤33Gy	Dmax ≤37.5Gy^b^ Dmax ≤40Gy^ab^	Dmax to 0.03 cc
Left & Right Optic nerve	–	Dmax ≤33Gy	Dmax ≤35Gy^b^	Dmax to 0.03 cc
Left & Right Orbits	–	Dmax ≤33Gy	Dmax ≤35Gy^b^	Dmax to 0.03 cc
Left & Right Lens	–	Dmax ≤6Gy	Dmax ≤10Gy^b^	Dmax to 0.03 cc

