Brain Stem	–	Dmax ≤33Gy	Dmax ≤37.5Gy^b^ Dmax ≤40Gy^ab^	Dmax to 0.03 cc
Left & Right Cochlear	–	Dmax ≤33Gy	Dmax ≤35Gy^a^	Dmax to 0.03 cc
Brain	Brain parenchyma down to cranial margin of dens	30Gy	–	–
PTV_Brain	(Brain + 3 mm isotropic margins) – (GTVall_5mm^b^ + HAZ)	95% of volume covered by 30Gy D2% ≤ 37.5Gy D98% (Dose to 98% of volume) ≥ 25Gy	90% of volume covered by 30Gy D98% ≥ 22.5Gy^b^ D2% ≤ 40Gy^b^	–

^a^*Applicable if tumours within/ ≤5 mm from OARs*^b^*Only applicable to HA-SIB-WBRT plans*

Patients whose plans are unable to meet the recommended constraints will not be eligible for the trial and will be dropped out and undergo WBRT or HA-WBRT as standard of care treatment. Patients can also voluntarily or involuntarily drop-out of the trial at any time after enrolment. These patients will not be replaced. The reason for drop-out must be recorded.

All treatment plans in the experimental arm will be reviewed and approved at the weekly Neuro-radiation oncology team audits prior to the start of treatment. Immobilisation will be performed in all patients. Daily image verification by image-guided radiotherapy is required.

All concomitant treatments should be documented. The use of concurrent cytotoxic systemic treatments is not allowed as this could cause additional or unexpected neuro-toxicities. If the participant is on systemic treatments, a treatment break of at least 7 days for immunotherapy or chemotherapy and 3 days for targeted therapy is recommended before and after radiotherapy. Interruptions should be discussed with the patient’s prescribing medical oncologist.

The use of dexamethasone during radiotherapy is not mandatory but is recommended for use if the patient with symptomatic brain metastases, significant cerebral oedema, large tumours or posterior cranial fossa lesions. The concurrent use of memantine for cognitive protection is recommended but not mandated.

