### Assignment of interventions

Patients recruited will be stratified by the number of brain metastases < 10 vs. ≥10. Within each stratum, patients will be randomized in a 1:1 ratio to control vs. experimental arms. Simple randomization will be performed using a computer-generated random sequence allocation. This will be performed by the research coordinator after informed consent has been taken. The allocation sequence is concealed from the investigators. Patients and treating radiation oncologist will not be blinded to the intervention as it was opined that our patients would want to be aware of the treatment received and that unblinding would not significantly affect our primary objective measure.

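### Contrast CT is allowed without condition for follow-up scans that determine an imaging primary endpoint, although every patient is MRI-eligible at entry

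*Protocol article*

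**What the plan says.** The rule is in the footnote to Table 3 (schedule of enrolment, interventions and assessments): "MRI is recommended for follow-up brain imaging but contrasted-CT scan is allowed". The visible text sets no condition for using CT, does not require one modality per patient, and does not require MRI confirmation of a CT read. The same footnote makes the schedule advisory.

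Other parts of the protocol article bear on this rule:

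- **Eligibility criteria, Table 1.** An exclusion criterion is "Contraindication to Gadolinium contrast-enhanced MRI brain", so every enrolled patient can have contrast MRI at entry.
- **Interventions, Table 2.** Gross tumour volumes are "Contoured using fused contrast enhanced MRI images", but those rows carry the footnote "Only applicable to HA-SIB-WBRT plans". The hippocampi are "Contoured using fused MRI as per RTOG contouring atlas", and the description in that row carries no such limit.
- **Primary endpoint.** "Response to treated lesions will be rated based on RANO-Criteria [19] or RECIST 1.1-Criteria".
- **Statistical analysis plans.** The endpoint is analysed as time from randomisation to target lesion progression. Patients who die without documented progression are censored at their last brain imaging, whatever its modality.
- **Assignment of interventions.** "Patients and treating radiation oncologist will not be blinded to the intervention", on the ground that "unblinding would not significantly affect our primary objective measure".
- **Secondary endpoints.** Uncertain or equivocal reads of target lesions go to a multi-disciplinary team, with advanced imaging or histology when needed.

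**The concern.** Target lesion progression is judged by comparing serial scans of 4 to 25 lesions per patient. When the modality changes between scans, a difference in apparent size mixes real change with a change of instrument. That can conceal growth, or produce apparent growth where there is none. Intracranial progression, a secondary endpoint that includes asymptomatic and distal lesions, is exposed in the same way.

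Modality is chosen after allocation is known. The argument for leaving the trial unblinded is that the primary measure is objective, and an unrestricted choice of scan weakens it. The multi-disciplinary review helps with doubtful comparisons, but progression that CT does not show produces no equivocal read to refer. Because the censoring rule does not distinguish modality, a CT that misses growth extends a patient's recorded time in control.

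At stake are the power of a small trial if misclassification is equal in the arms, and the validity of the comparison if it is not.

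**Working it through.** **1. The plan's own figures.** The Sample size section gives 50% control at 6 months in the HA-WBRT arm, a hazard ratio of 0.27, 30 evaluable patients per arm, 80% power, a two-sided 5% log-rank test and 40% non-evaluable.

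- Experimental control rate: 0.50^0.27 = 0.829, which agrees with the stated 83%.
- Total: 60 / (1 − 0.40) = 100, as stated.
- Power: a log-rank simulation (exponential times, 30 per arm, follow-up to 6 months, 20,000 runs) gives 80.05%.
- Expected events by 6 months: 30 × 0.50 + 30 × 0.171 = 15 + 5.1 ≈ 20.

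The sample size is reproduced and is not in question.

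**2. Assumptions.** The documents give neither the share of patients followed by CT (c) nor the sensitivity of CT relative to MRI (s). Illustrative ranges are c = 10% in one arm against 30–50% in the other, and s = 60–80%. Only missed progression is modelled here. False progression on CT would need a further assumption and could move the result either way.

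**3. Unequal CT use, no true effect.** With 50% true progression by 6 months in both arms, recorded progression = 0.5 × [1 − c(1 − s)]. The spurious HR is ln(1 − progression in the high-CT arm) / ln(1 − progression in the low-CT arm).

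| c (low vs high) | s | Recorded progression | Spurious HR |
|---|---|---|---|
| 10% vs 30% | 0.6 | 0.48 vs 0.44 | 0.89 |
| 10% vs 30% | 0.8 | 0.49 vs 0.47 | 0.94 |
| 10% vs 50% | 0.6 | 0.48 vs 0.40 | 0.78 |
| 10% vs 50% | 0.8 | 0.49 vs 0.45 | 0.89 |

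For example, ln(0.60)/ln(0.52) = 0.511/0.654 = 0.78. In simulation with 30 per arm, the two-sided false-positive rate stays at about 5–6% in three of these scenarios and reaches about 9% in the one with HR 0.78.

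**4. Equal misses, true HR 0.27.** The same simulation gives power of 80% with nothing missed, 74% with 10% of progressions missed and 66% with 20% missed. The fraction missed is c(1 − s). CT for 30–50% of patients in both arms therefore means between 0.30 × 0.20 = 6% and 0.50 × 0.40 = 20% missed. At 10% CT use in both arms, 2–4% are missed and power is about 77–79%.

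**5. Misses only in the control arm, true HR 0.27.** Power is 67% with 10% missed and 52% with 20% missed. Unequal misses can thus work against the experimental arm as well as for it.

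**The case against.** The strongest defence is that this is a disclosed, pragmatic choice. The footnote follows routine practice, MRI is the recommended scan, and doubtful reads go to a multi-disciplinary team. A CT may also be better than no scan in a trial that already assumes 40% non-evaluable. If CT is rare, little is lost: at 10% use in both arms power barely moves, and three of the four unequal scenarios leave the false-positive rate near 5–6%. The visible text is also incomplete, since the body of Table 3 is not shown.

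Much of this stands as a limit on size. It does not remove the unconditional permission, and the team review cannot recover progression that was never seen.

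A reader might infer several stronger points that the documents do not support:

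- *That target lesions are drawn on MRI in both arms.* The tumour-volume rows apply to HA-SIB-WBRT plans only. For the control arm, the text shows planning MRI only through the hippocampal contours.
- *That the unblinded treating oncologist reads the endpoint scans.* The article says this person is unblinded but does not name the reader.
- *That most lesions are small.* No size distribution is given, and lesions up to 5 cm are admitted.
- *That CT can only hide progression, so the bias has a known direction.* A comparison across modalities can also create false progression, and nothing says which arm would have more CT.

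**Conclusion.** The concern holds as a weakness in a stated rule. Following the footnote as written allows mixed-modality data for an imaging primary endpoint in an open-label trial with about 20 expected events, although every patient could have MRI at entry. Equal misses cost power, and use that differs by arm can bias the result. The spurious HR of 0.78–0.94, and power of about 66–76% when 30–50% of both arms are followed by CT, depend wholly on assumed CT share and sensitivity. They illustrate what the rule permits and do not estimate what will happen. The change is worth making because it is cheap; no error in the sample size is implied.

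**What to change.** - Make contrast MRI the required modality for primary-endpoint assessments in both arms. Allow CT only for a documented reason, for example an MRI contraindication that arises after entry, or an emergency.
- Record the modality of every follow-up scan and report it by arm. As recruitment is under way (Trial status section), do the same for scans already taken.
- Treat CT symmetrically. Seek MRI confirmation of a CT read whether or not it shows progression, and keep CT reads in the primary analysis under the existing censoring rule. Discarding negative CTs while counting unconfirmed positive ones would inflate recorded progression.
- Add a sensitivity analysis that uses MRI assessments only, for both events and censoring.

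The cost is a small amendment, with the sample size unchanged at 60 evaluable and 100 in total. A minority of CT follow-ups would become MRI. Some patients who would have had a CT may miss a scan, and the documented-reason fallback limits that loss.

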### Sample size

Assuming a 6-month target lesion control rate of 50% in the HA-WBRT arm, we will need 60 subjects (30 per arm) to detect a hazard ratio of 0.27 [9] between the 2 arms with 80% power using a 2-sided log-rank test at 5% significance level. A hazard ratio of 0.27 means the 6-month target lesion control rate in the HA-SIB-WBRT arm is expected to be 83%. These calculations assume that subjects will be followed up till target lesion progression, or for a minimum of 6 months. Assuming a 40% non-evaluable rate, an estimated total sample size of 100 subjects will be required.

### Assignment of interventions

Patients recruited will be stratified by the number of brain metastases < 10 vs. ≥10. Within each stratum, patients will be randomized in a 1:1 ratio to control vs. experimental arms. Simple randomization will be performed using a computer-generated random sequence allocation. This will be performed by the research coordinator after informed consent has been taken. The allocation sequence is concealed from the investigators. Patients and treating radiation oncologist will not be blinded to the intervention as it was opined that our patients would want to be aware of the treatment received and that unblinding would not significantly affect our primary objective measure.

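### Allocation is stratified by number of metastases but named as simple randomisation, so neither arm size nor the stratification factor is assured to be balanced

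*Protocol article*

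**What the plan says.** Three statements in the Assignment of interventions section belong together. The factor: "Patients recruited will be stratified by the number of brain metastases < 10 vs. ≥10". The ratio: "Within each stratum, patients will be randomized in a 1:1 ratio to control vs. experimental arms". The method: "Simple randomization will be performed using a computer-generated random sequence allocation". No block, minimisation or other restriction is mentioned.

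The Sample size section plans equal arms: "we will need 60 subjects (30 per arm) to detect a hazard ratio of 0.27", "with 80% power using a 2-sided log-rank test at 5% significance level". It raises the total to 100 for a 40% non-evaluable rate.

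In the Statistical analysis plans section, the sentence on the primary comparison names a two-sided log-rank test and no stratification. A later, general sentence on time-to-event endpoints says that log-rank tests and Cox models will adjust for number of metastases. The same section compares the proportions with cognitive, quality-of-life and functional deterioration by Fisher's exact test, without adjustment.

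**The concern.** Stratifying an allocation balances a factor only if allocation is restricted inside each stratum, for example by permuted blocks. Simple randomisation is the unrestricted case: each patient's arm is an independent draw. Splitting patients into strata before making independent draws changes nothing. The article therefore claims a design feature and then names a method that does not provide it. This is a stated method that does not do what is claimed for it, not a detail left to a fuller document.

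Number of metastases is the only factor the sponsor chose to control by design, and the trial is small: about 19 to 20 target lesion progressions under its own assumptions. At stake are the credibility of the baseline comparison, a little power, and the unadjusted secondary comparisons in a trial that happens to draw an uneven split.

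**Working it through.** **1. The plan's own sample size.** Inputs from the Sample size section: "Assuming a 6-month target lesion control rate of 50% in the HA-WBRT arm"; hazard ratio 0.27; 80% power; two-sided 5%; "subjects will be followed up till target lesion progression, or for a minimum of 6 months".

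- Experimental control rate: 0.5^0.27 = 0.829. This agrees with the statement that "the 6-month target lesion control rate in the HA-SIB-WBRT arm is expected to be 83" per cent.
- Events (Schoenfeld, 1:1): 4 × (1.960 + 0.842)² / (ln 0.27)² = 18.3, rounded up to 19.
- Mean six-month event probability: (0.500 + 0.171) / 2 = 0.335.
- Patients: 19 / 0.335 = 57, or 58 in equal arms. The stated 60 is reproduced to within 2.
- Inflation: 60 / (1 − 0.40) = 100, as stated.

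**2. Why the strata have no effect.** Suppose m of the 100 patients have 10 or more lesions. With independent 1:1 draws inside strata, the number of these in the experimental arm is Binomial(m, 0.5), and the number of the others in that arm is an independent Binomial(100 − m, 0.5). Without strata, each patient is still an independent 1:1 draw, so both distributions are the same. Simulation (400,000 trials per setting) agrees: with 40% in the upper stratum, the share differs by at least 10 points in 31.1% of trials with strata and 31.0% without.

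**3. Arm size (exact binomial, probability 0.5).**

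| Patients | Split | Probability |
|---|---|---|
| 100 | exactly 50:50 | 8.0% |
| 100 | 55:45 or worse | 36.8% |
| 100 | 60:40 or worse | 5.7% |
| 60 | exactly 30:30 | 10.3% |
| 60 | 36:24 or worse | 15.5% |

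**4. Balance of the factor.** The article does not say what share of patients will have 10 or more lesions, so a range of 20 to 50% is assumed.

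| Assumed share | Arms differ by ≥10 points | Arms differ by ≥15 points |
|---|---|---|
| 20% | 21.6% | 6.3% |
| 30% | 27.9% | 10.3% |
| 40% | 31.1% | 12.8% |
| 50% | 32.3% | 13.5% |

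A hand check at 40%: the standard error of the difference with 50 per arm is √(0.4 × 0.6 × 2/50) = 0.098, so 10 points is 1.02 standard errors, a two-sided probability of about 31%.

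**5. What restriction would give.** With blocks of 4 (an illustration), each stratum can be out by at most 2 patients, so the arms differ by at most 4 in total and the share by at most 4 points. Under simple randomisation the 95th percentiles are a 20-patient difference (60:40) and 16 to 20 points.

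**6. Power.**

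- Arm size alone: Schoenfeld power with 60 patients (60 × 0.335 = 20.1 events) is 83.6% at 1:1 and 82.0% at 60:40. Averaged over simple randomisation it is 82.9%, a cost of 0.7 points.
- Imbalance in a prognostic stratum as well: simulations assumed 60 patients, 40% in the upper stratum, a stratum hazard ratio of 2 to 3 and a treatment hazard ratio of 0.4. None of these assumptions except the 60 comes from the article. Blocking raised the power of the unadjusted log-rank test by under 1 point with six-month follow-up and by about 1.5 to 2.5 points with 12 months. At the planned hazard ratio of 0.27 the gain was 1 to 2 points.
- Under the null hypothesis, the unadjusted test with simple randomisation rejected in 5.0 to 5.5% of trials.

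**The case against.** The strongest reply is that little is lost. Simple randomisation is valid: both arm size and the factor are balanced in expectation, and chance imbalance is already allowed for in the p-value. The analysis section also plans adjustment for number of metastases in time-to-event comparisons. In the simulations at hazard ratio 0.4 with 12-month follow-up, a stratified log-rank test under simple randomisation reached 73.7 to 74.4% power, against 67.6 to 73.3% for blocking with the unadjusted test. Adjustment thus recovers more than blocking does. In an open-label, single-centre trial, unrestricted allocation also has the merit of being unpredictable. The word 'simple' may be loose, and the full protocol may specify blocks.

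Most of this stands, and it limits the consequence. It does not remove the inconsistency. If unpredictability were the reason for simple randomisation, there would be no reason to stratify the allocation. If blocks are used, the article describes the method wrongly. The adjustment is not named in the sentence that defines the primary test, and the Fisher's exact tests have none.

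A reader might infer three stronger things: that the arms will be unbalanced, that the primary comparison is biased, or that power suffers materially. The documents support none of them. What is lost is the assurance of balance; the type I error holds, and the power cost is about 0 to 2 points. Nor would blocking all 100 patients fix the split among whichever 60 prove evaluable.

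**Conclusion.** The point holds as an inconsistency of method: the stated stratification cannot do its work under the stated randomisation. The law of the imbalance and the arm-size probabilities are exact and need no assumption beyond independent 1:1 draws. The probabilities for the factor rest on an assumed 20 to 50% of patients having 10 or more lesions. The power figures rest on the further assumptions listed with them. Severity is minor to moderate: validity is not threatened, but there is a material chance of a visible imbalance in the one factor chosen for control, and the protection offered by the analysis is not clearly attached to the primary test.

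**What to change.** First establish which method is in use.

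- **If allocation is truly simple:** for the remaining patients, generate a new list with permuted blocks of randomly varying size within each of the two strata. It should be prepared outside the study team, with block sizes withheld from recruiting staff. Patients already randomised keep their allocation.
- **If blocks are already used:** replace the word 'simple' with a description of the actual method.
- **In either case:** state in the sentence defining the primary comparison that the log-rank test is stratified by number of metastases (fewer than 10 versus 10 or more).

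The cost is a short amendment and, in the first case, a new list. The sample size and its assumptions do not change. The drawbacks are slight predictability near block ends in an open-label, single-centre trial, limited by varying and undisclosed sizes, and a benefit confined to patients still to be recruited; the Trial status section says recruitment is ongoing. If the sponsor prefers unrestricted allocation, the alternative is to drop the claim of stratified allocation and rely on the stratified analysis.
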